### General procedures

All participating patients, regardless of the study arm into which they are randomized, will be monitored and managed following general standard of care practices aimed at maintaining optimal conditions. Both intraoperative and immediate-postoperative (3 h) anesthetic management (unrelated to ventilatory management) will be decided by the attending physician as they see fit, following the established protocols at each center. However, in order to ensure a high standard of anesthetic management, a number of common strategies have been established: halogenated agents will be given to maintain anesthesia, intra- and postoperative pain will be controlled with neuraxial anesthetics, hemodynamic management will be based on advance cardiac output monitoring, and fluids will be administered following goal-direct therapy principles. Appropriate antibiotic prophylaxis will be administered, and pharmacological prevention of postoperative nausea and vomiting (PONV) will be adopted. Finally, when nasogastric tube insertion is required, it should be withdrawn prior to extubation when possible. All these data will be collected and analyzed.

### Monitoring

Intraoperative monitoring will include an electrocardiogram (ECG), pulse oximetry, capnography, bladder or esophageal temperature, anesthetic depth analysis (bispectral analysis, BIS) and a neuromuscular blockade (with train of four, TOF), invasive blood pressure measurements, and advanced hemodynamic monitoring with minimally invasive monitoring (optional depending on the standard clinical practice and availability of equipment at each hospital). Ventilatory parameters will be monitored by the anesthesia machine: VT, PEEP, FiO_2_, peak airway pressure (P_aw_), plateau pressure (P_plat_), and dynamic compliance of the respiratory system (C_rs_). Intra-abdominal pressure (IAP) will be monitored during laparoscopic surgery. Postoperative monitoring will include at least an ECG, pulse oximetry, and invasive arterial pressure measurements.

### General intraoperative ventilator management

Pre-oxygenation will be performed for 5 min at FiO_2_ 0.8 with a tightly sealed face mask before induction. Patients will be ventilated in volume control mode (VCV) with squared flow, a VT of 8 ml/kg of the predicted body weight (PBW), and a P_plat_ of ≤25 cmH_2_O. If the P_plat_ reaches or exceeds 25 cmH_2_O, VT will be decreased in 1 ml/kg steps until the P_plat_ drops to ≤25 cmH_2_O. The respiratory rate (RR) will be set to maintain an end-tidal carbon dioxide partial pressure (EtCO_2_) between 35–45 mmHg, with an inspiratory to expiratory ratio (I:E) of 1:2 and a inspiratory pause time of 20% of the inspiratory time. FiO_2_ will be set at 0.8 throughout the whole procedure. During the awakening period from general anesthesia (patients with spontaneous ventilation), a FiO_2_ of 0.8 will be applied at the same end-expiratory pressure used, using either PEEP or CPAP.

Extubation will not be allowed by applying a positive pressure above the previously set PEEP or CPAP or while suctioning through the tracheal device. If necessary, aspiration can be performed at least 10 min before extubation. After suction, the patient will be switched back to mechanical ventilation. If the patient is randomized into the individualized perioperative or individualized intraoperative + postoperative CPAP group, a new alveolar recruitment maneuver will be performed. Once extubation has been performed, the patient will be oxygenated with 0.5 FiO_2_ through a Venturi mask.

### Specific intraoperative ventilatory management

The intraoperative ventilatory management comprises a two-arm management strategy (Figure 1).

#### Standard group

The patients will be ventilated as previously described in the General intraoperative ventilator management section.

#### Individualized group

In this group, an ARM is performed after intubation followed by a PEEP titration trial. Before the recruitment is performed the anesthesiologist must ensure that there is hemodynamic stability [mean arterial pressure (MAP) of more than 70 mmHg and/or a cardiac index of more than 2.5 ml/min/m^2^] for at least 5 min, a stroke volume variation (SVV) of less than 10%, and an adequate neuromuscular blockade (0 of 4 by TOF). The ARM is performed as described in the following section.

### Alveolar recruitment maneuver (ARM)

The ventilator will be changed from VCV to pressure-controlled ventilation (PCV) with a 20-cmH_2_O driving pressure and an RR of 15 breaths per minute (rpm), I:E of 1:1, 0.8 FiO_2_, and PEEP of 5 cmH_2_O. For the recruitment phase, the PEEP level will be increased in steps of 5 cmH_2_O every ten respiratory cycles, up to a PEEP of 20 cmH_2_O, to produce an airway opening pressure of 40 cmH_2_O and maintained for 15 respiratory cycles in the opening pressure [32] (total maneuver time: 180 s). If hemodynamic instability appears during the recruitment phase (a >50% decrease in the cardiac index or MAP), the maneuver will be interrupted and 5–15 mg ephedrine or 0.05-0.15 mg phenylephrine given; after hemodynamic stabilization, a new ARM will be performed. After lung recruitment is accomplished, the optimal PEEP is titrated through a decremental PEEP trial, as described in the following section [8] (Figure 2).

**Figure 2 Fig2:**
[figure not shown]
Alveolar recruitment maneuver and PEEP titration trial protocol. *RM* recruitment maneuver, *Crs* respiratory system compliance, *PEEP* positive end-expiratory pressure, *CPAP* continuous positive end-expiratory pressure, *VCV* volume-controlled ventilation, *PCV* pressure-controlled ventilation, *RR* respiratory rate, *I:E* inspiratory-to-expiratory ratio.

### Titration of the optimal individual positive end-expiratory pressure: Decremental PEEP trial

At the end of the last step of the PCV recruitment phase when the PEEP is 20 cmH_2_O, the mode will be switched to VCV with a VT of 8 ml/kg, RR of 15 rpm, and I:E of 1:2, 0.8 FiO_2_. After this, PEEP is decreased 2 cmH_2_O steps every 30 s until the highest C_rs_ observed on the ventilator’s monitor (until C_rs_ starts decreasing or does not increase). Once the best C_rs_ is known, a new recruitment maneuver is performed and the PEEP for the best C_rs_ + 2 cmH_2_O is adjusted. In the case of accidental airway depressurization, a new ARM is performed while an identical PEEP is set (Figure 2).

The need for new recruitment maneuvers and a PEEP trial is evaluated every 40 min by measuring the C_RS_ and peripheral capillary oxygen saturation (SpO_2_). If there is a drop of more than 10% of the C_rs_, FiO_2_ will be transitorily decreased to 0.21-0.25 for at least 4 min, and if SpO_2_ drops to ≤96% at this FiO_2_, a new recruitment and PEEP trial are performed.

### Intraoperative rescue maneuvers

In the case of arterial hypoxemia (SpO_2_ of ≤95% with FiO_2_ 0.8), after excluding endobronchial tube displacement, bronchospasm, pneumothorax, or a hemodynamic cause, a protocol for rescue therapy has been devised for each specific group.

#### Individualized group

A new recruitment maneuver and PEEP trial are performed. If SpO_2_ is less than 95%, FiO_2_ is increased in 0.1 steps.

#### Standard group

The 0.1 FiO_2_ is increased until SpO_2_ is more than 95%. If arterial hypoxemia persists with 1.0 FiO_2_, the PEEP is increased in steps of 2 cmH_2_O (until a maximum of 12 cmH_2_O).

### General postoperative management in the postoperative care unit

General postoperative management in the postoperative care unit (PACU) not related to ventilator management will be decided by the attending physician following the established protocols at each center. Patients will be oxygenated with FiO_2_ 0.5 through a Venturi mask for the first 15 min. The arterial oxygenation will be evaluated 15 to 30 min later when patients are awake and collaborative [Glasgow coma score (GCS) higher than 13] without any residual anesthetic effect (Richmond scale −1 to +1) and under pain control [verbal analog pain scale (*echelle verbal analogique*; EVA) score <4] by decreasing the FiO_2_ to 0.21 for at least 5 min (air test). The air test is intended to identify possible decreases in SpO_2_ related to postoperative atelectasis that may have been masked by the use of 0.5 FiO_2_. The air test is not performed if the patient already has an SpO_2_ below 96% with FiO_2_ 0.5. Air tests are repeated at 60, 120, and 180 min after PACU admission in all study patients. When the patient arrives in the PACU or ICU with invasive mechanical ventilation, the above-mentioned management will be applied after extubation.

### Specific postoperative ventilatory management

Postoperative ventilatory management consists of two types of management for each of the two intraoperative arms (Figure 1).

#### Individualized perioperative group

Supplemental oxygen at FiO_2_ 0.5 will be delivered through a Venturi mask. If SpO_2_ falls below 96% during the room-air test (FiO_2_ 0.21 for 5 min), a CPAP of 5 cmH_2_O (or 10 cmH_2_O if the BMI exceeds 30) with FiO_2_ 0.5 will be initiated. Reevaluation of arterial oxygenation will be performed every hour for the first 3 postoperative hours. If patients require CPAP at any time during their PACU stay, it will be maintained for 3 h, independently of their oxygenation levels.

#### Individualized intraoperative + postoperative CPAP group

A CPAP of 5 cmH_2_O (or 10 cmH_2_O if the BMI exceeds 30) with a FiO_2_ 0.5 will be applied to all patients in this group.

#### Standard + postoperative CPAP group

A CPAP of 5 cmH_2_O (or 10 cmH_2_O if the BMI exceeds 30) with a FiO_2_ 0.5 will be applied to all patients in this group.

#### Standard group

Supplemental oxygen at 0.5 FiO_2_ will be delivered through a Venturi mask.

If any patient in any group experiences PONV or does not tolerate the CPAP device, they will be changed to standard therapy.

### Postoperative rescue maneuver

Rescue therapies are initiated if the SpO_2_ decreases to 92% or less during the air test or if SpO_2_ is 95% or less while on 0.5 FiO_2_, with or without pressurization according to the patient’s randomized group. Evaluation of a positive or negative response to the rescue maneuver is performed in a maximum period of 30 min.

Individualized perioperative group: For patients with a 0.5 FiO_2_ Venturi mask, the rescue maneuver is started with 5 cmH_2_O CPAP (or 10 cmH_2_O if the BMI exceeds 30). If the patient is already on 5 cmH_2_O CPAP, it will be increased to 10 cmH_2_O. In patients with a BMI exceeding 30 or with persistent hypoxemia and/or hypercapnia [blood partial pressure of carbon dioxide (PaCO_2_) >50 mmHg with a pH <7.30], tachypnea (RR >25 rpm), or increased activity of accessory respiratory muscles are present, inspiratory support with noninvasive ventilation (NIV) will be started.

Individualized intraoperative + postoperative CPAP and Standard + postoperative CPAP group: CPAP will be increased to 10 cmH_2_O in all cases. In patients with a BMI of more than 30 or persistent hypoxemia and/or hypercapnia (PaCO_2_ > 50 mmHg with a pH <7.30), tachypnea (RR >5 rpm), or increased activity of accessory respiratory muscles are present, inspiratory support with NIV will be started.

Standard group: FiO_2_ will be increased to 0.8 through a controlled FiO_2_ mask with a reservoir bag. If there is persistent hypoxemia, CPAP of 5 cmH_2_O (or 10 cmH_2_O if the BMI exceeds 30) will be used. If hypoxemia persists, CPAP will be increased to 10 cmH_2_O. If persistent hypoxemia and/or hypercapnia (PaCO_2_ > 50 mmHg with a pH <7.30), tachypnea (RR exceeding 25 rpm), or increased activity of accessory respiratory muscles are present, inspiratory support with NIV will be started.

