### Study variables

The primary outcome of the iPROVE trial is a composite of pulmonary and systemic complications experienced by the study population in the first 7 days after surgery and can be divided into respiratory complications and systemic complications as discussed below.

Respiratory complications:Atelectasis: defined by a combination of SpO_2_ ≤ 96% during the air test and chest X-ray images suggesting lung opacities with a shift in the mediastinum, hilum, or hemidiaphragm toward the affected area and compensatory overinflation in the adjacent non-atelectic lung. Hypoxemia: defined as SpO_2_ of 92% or less with 0.21 FiO_2_ or SpO_2_ of 95% or less with 0.5 FiO_2_. ARDS: according to the Berlin definition [33]. Pneumonia: the presence of a new pulmonary infiltrate and/or progression of previous pulmonary infiltrates on a chest radiograph plus at least two of the following criteria: (a) leukocytosis with >12,000 WBC/mm^3^ or leukopenia with <4000 WBC/mm^3^, (b) fever >38.5°C or hypothermia <36°C, and (c) increased secretions with purulent sputum and a positive bronchial aspirate. Pleural effusion: chest x-ray with the presence of costophrenic angle blunting, displacement of adjacent anatomical structures, and blunting of the hemidiaphragmatic silhouette in the supine position. Bronchospasm: presence of expiratory wheezing treated with bronchodilators. Pneumothorax: air in the pleural space and the mediastinum is shifted to the opposite side (a thorax radiography will be performed in suspected cases of auscultation hoarseness). Aspiration pneumonitis: respiratory failure after the inhalation of regurgitated contents. Requirements for rescue maneuvers: increased FiO_2_, increased requirement for CPAP, or the need for noninvasive or invasive ventilation. Early extubation failure or requirement of reintubation.

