### Statistical analysis

The sample size was estimated from the literature, assuming a risk of 25% for developing postoperative pulmonary or non-pulmonary complications [17], a relative reduction of 50% in the incidence of these complications with individualized alternative treatment in the groups, and taking into account the statistical power for making matched comparisons between the four groups in the study [37]; using a significance level of 5% and a power of 80% results in a total requirement of 920 patients (230 in each ventilatory management group). This figure was enlarged to 1012 (10%) to compensate for possible dropouts. The recruitment among centers will be competitive.

First, the patient baseline variables will be described and the homogeneity of these groups evaluated using appropriate statistical tests for the type of variable being analyzed (mean difference of proportions, chi-square, ANOVA, with a corresponding confidence interval of 95%). Then bivariate associations between patient characteristics, the primary endpoint, and the secondary outcomes will be performed by calculating their respective odds ratios or, in the case of a quantitative outcome, by an ANOVA test.

Following this, the association between the intervention groups and the main and secondary outcomes will be analyzed, calculating the corresponding odds ratio, or ANOVA in the case of quantitative outcomes. In all cases, respective means or proportions are estimated with their respective 95% confidence intervals. The primary outcome, pulmonary complications outcome, non-pulmonary complications, and mortality measurement analyses will be repeated using multivariate logistic regression models and adjusted to any patient characteristics that are shown to be clinically relevant by the previous bivariate analyses. Similarly, a multilevel analysis will be performed, incorporating different hospitals as random effects in order to assess whether the recruitment center influenced the results.

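### The respiratory-rate trigger for NIV during rescue is printed as above 5 rpm in the two postoperative-CPAP arms and above 25 rpm in the other two, almost certainly a dropped digit

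*Protocol article*

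**What the plan says.** The section 'Postoperative rescue maneuver' sets a common entry rule and then an escalation path for each arm. Entry is by oxygen saturation: "Rescue therapies are initiated if the SpO_2_ decreases to 92% or less during the air test or if SpO_2_ is 95% or less" on FiO2 0.5. The response is then assessed: "Evaluation of a positive or negative response to the rescue maneuver is performed in a maximum period of 30 min".

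The last step of each path is NIV, and the tachypnea criterion for it is stated three times:

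- Individualized perioperative group (group 1): "tachypnea (RR >25 rpm), or increased activity of accessory respiratory muscles are present, inspiratory support with noninvasive ventilation (NIV) will be started".
- Groups 2 and 3 (CPAP for all after surgery, following individualized and standard intraoperative ventilation respectively; one shared paragraph): "tachypnea (RR >5 rpm), or increased activity of accessory respiratory muscles are present, inspiratory support with NIV will be started".
- Standard group (group 4): "tachypnea (RR exceeding 25 rpm", followed by the same accessory-muscle criterion and the same action.

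**The concern.** The three statements have the same structure and differ in one number. The criterion is labelled tachypnea in each, yet in groups 2 and 3 the cut-off lies far below a normal breathing rate.

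This is a bedside treatment rule, so the number decides who receives NIV. The criteria are joined by 'or', so meeting the respiratory-rate criterion alone is enough. Taken literally, nearly every spontaneously breathing patient in rescue in groups 2 and 3 qualifies, including one whose hypoxemia has been corrected by CPAP 10 cmH2O. The response assessment would then no longer separate patients who need escalation to NIV from those who do not.

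The discrepancy also follows the randomization. Both CPAP arms carry 5 rpm and both other arms carry 25 rpm. Each pair that shares an intraoperative strategy (1 versus 2, 3 versus 4) therefore sets a 25-rpm arm against a 5-rpm arm. If sites followed the text, NIV use among rescued patients would differ between these arms partly because of a misprint, and some patients would receive NIV they do not need.

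**Working it through.** **1. The NIV criteria side by side** (all from 'Postoperative rescue maneuver')

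| Criterion | Group 1 | Groups 2 and 3 | Group 4 |
|---|---|---|---|
| Persistent hypoxemia | yes | yes | yes |
| PaCO2 >50 mmHg with pH <7.30 | yes | yes | yes |
| Accessory-muscle activity | yes | yes | yes |
| BMI above 30 | yes | yes | not listed |
| Respiratory rate | >25 rpm | **>5 rpm** | >25 rpm |

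Between group 1 and groups 2 and 3, the respiratory rate is the only NIV criterion that differs.

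**2. Is 5 rpm plausible as an intended value?** The article offers two reference points. 'Alveolar recruitment maneuver (ARM)' sets a controlled rate of 15 rpm. The SIRS definition under 'Study variables' uses a rate above 20 rpm as a raised value. A cut-off of 5 rpm is a third of the first and a quarter of the second, so it cannot mark tachypnea. No section gives a reason for a separate threshold in the CPAP arms. The only value the article supports is 25 rpm, printed in the paragraphs immediately before and after. That a digit was dropped is an inference, but a strong one.

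**3. Does it change the composite outcomes?** Under 'Study variables' one respiratory component is "Hypoxemia: defined as SpO_2_ of 92% or less with 0.21 FiO_2_ or SpO_2_ of 95% or less with 0.5 FiO_2". These cut-offs are the same as those for entering rescue. A rescue maneuver is also a respiratory component in its own right. A patient who reaches the NIV decision has therefore already been counted, and extra NIV adds about 0 events to the primary composite or the 7-day pulmonary composite. The criteria for intubation after 1 h of NIV, under 'Invasive ventilation', do not use respiratory rate.

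**4. How many patients could be affected?** No rescue rate is given, so the number cannot be computed. An upper bound follows from step 3: every rescued patient is a primary event, so the rescue rate cannot exceed the composite rate.

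Inputs from 'Statistical analysis': "assuming a risk of 25% for developing postoperative pulmonary or non-pulmonary complications"; a relative reduction of 50%; 230 patients per group before the dropout allowance; 1012 patients in total.

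- Randomized per group: 1012 / 4 = 253. Groups 2 and 3 together: 2 × 253 = 506.
- Before the dropout allowance: 2 × 230 = 460.
- Reduced risk: 0.25 × (1 − 0.50) = 0.125.

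| Composite risk in groups 2 and 3 | Of 506 | Of 460 |
|---|---|---|
| 25% | 0.25 × 506 = 126.5, at most 126 | 0.25 × 460 = 115 |
| 12.5% | 0.125 × 506 = 63.25, at most 63 | 0.125 × 460 = 57.5, at most 57 |

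These bound the number of rescued patients. Excess NIV use is smaller, because rescued patients with BMI above 30, persistent hypoxemia, hypercapnia, accessory-muscle use or a rate above 25 rpm would receive NIV under the correct rule as well.

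**The case against.** The strongest reply is that the misprint corrects itself. The number explains the word tachypnea, the right value stands in the neighbouring paragraphs, and few clinicians would treat six breaths per minute as fast. The article is also a condensed document. The section 'Trial organization' mentions an investigator manual and an e-CRF, which are not shown, and nothing at hand indicates that 5 rpm reached a site. A character lost in printing or in text extraction cannot be excluded either, though nothing points to it. All this stands as a reason to expect little practical harm. It is not a reason to leave a wrong number in a treatment rule.

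A second reply is that the routes to NIV differ by arm by design. The standard arm passes through FiO2 0.8, then CPAP of 5 cmH2O (10 if BMI exceeds 30), then 10 cmH2O, and has no BMI criterion for NIV. The CPAP arms go straight to 10 cmH2O. This is correct: NIV use in groups 3 and 4 would not be fully comparable even with 25 rpm throughout. The misprint adds to that difference and does not create it. Between groups 1 and 2, however, it is the only difference in the NIV criteria.

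Third, the response assessment would not become wholly idle, since response can still be judged once NIV is running. That is fair. What is lost is its role in deciding who moves to NIV.

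Finally, the ceilings depend on a planning risk taken from a literature source whose outcome definition cannot be checked here, and they apply one risk to two arms with different intraoperative strategies. They should be read only as conditional bounds.

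**Conclusion.** The concern holds. The article prints an impossible tachypnea threshold for two of the four arms, with no justification or correction elsewhere, and 25 rpm is the only value its own text supports.

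The consequence lies in the delivered rescue treatment and its comparability between arms. The primary result is not threatened: added events in the primary and 7-day pulmonary composites are about 0, and no sample size, power or significance level changes. Rescued patients in groups 2 and 3 could number at most 126 of 506 at the planned 25% risk, or 63 of 506 at 12.5%. Those bounds hold only if the planning risks apply to the composite as defined, and the excess NIV use would be lower still. Whether any patient would be treated differently depends on what the site documents say, which cannot be seen here. It should be corrected because it is a treatment trigger and the correction is trivial.

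**What to change.** In 'Postoperative rescue maneuver', in the paragraph for the two postoperative-CPAP groups, replace the threshold of 5 rpm with 25 rpm, so that one respiratory-rate criterion applies in all four arms. Confirm that the investigator manual and the e-CRF carry 25 rpm, and send the sites a short note.

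The cost is a one-figure correction, one document check and one notice. Nothing in the design or the analysis needs to change.

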### Noninvasive ventilation (NIV)

The ventilator (specific for NIV or with software for NIV) and interface for NIV will be chosen by the attending physician and based on hospital availability. CPAP, i.e., expiratory positive airway pressure (EPAP), and FiO_2_ will be set according to the patient’s randomized group. Positive pressure will start with an inspiratory positive airway pressure (IPAP) of 5 cmH_2_O higher than the EPAP and will be increased in steps of 5 cmH_2_O up to 15 cmH_2_O. The EPAP will be increased to a maximum of 10 cmH_2_O (15 cmH_2_O if the BMI exceeds 30).

